Participants can initiate, discontinue, and restart PrEP at any point during the study period. Changes to PrEP use can be communicated during any study visit, via weekly SMS surveys, or can be communicated to study staff outside of study visits. Reasons for discontinuing PrEP are recorded. Participants who restart PrEP after more than 2 weeks cessation must be rescreened. Study investigators consider someone stopped on PrEP if the participant’s weekly SMS adherence measures indicate that he/she had 2 consecutive weeks with 0 to 3 doses taken, or if the participant has >16 pills remaining from the month during a medication pickup. PrEP rescreening includes HIV testing and an assessment of willingness to commit to PrEP adherence. Participants who stop PrEP may continue in the study and continue with their remaining quarterly study visits. Participants who permanently stop PrEP or who do not want to immediately restart PrEP are instructed to return all Truvada as soon as possible.

Participants who seroconvert during the study period complete a close-out survey, receive facilitated referral to care with assistance by the case manager or site coordinator at each site, are discontinued from the study and do not attend subsequent study visits.

**Table 1 table1:** Description of quarterly and semiannual study visits for the Combination Prevention Effectiveness Study for cisgender men who have sex with men and transgender women, Thailand.

Study visit	Description
Quarterly study visits (every 3 months)	Confirm participant contact and locator information Administer CASI^a^ behavioral questionnaire Assess participant experience and impacts of study participation (including adverse events and social harms) Screen for signs and symptoms of acute HIV infection Provide HIV testing (including pooled NAAT^b^ testing if the participant has symptoms of acute HIV infection) Collect DBS^c^ for storage Distribute condom and lubricant
Semiannual study visits (every 6 months)	All procedures conducted at quarterly study visits Syphilis testing Rectal swab collection for rectal gonorrhea and chlamydia testing Serum creatinine measurement and estimated creatinine clearance calculation (for participants on PrEP^d^)

^a^CASI: computer-assisted self-interview.

^b^NAAT: nucleic acid amplification test.

^c^DBS: dried blood spots.

^d^PrEP: pre-exposure prophylaxis.

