In marginal structural models, inverse probability of treatment and censoring weights (IPTCWs) will be used in weighted, pooled logistic regression models of HIV infection. The data for each participant are structured such that each record represents 1 person-week of time either on PrEP or not on PrEP [39]. The odds ratio from the weighted, pooled regression provides an estimate of the hazard ratio for HIV infection associated with PrEP initiation similar to Cox time-dependent regression [41,42]. The IPTCWs at time *t_i_* incorporate the estimated probability of the observed treatment history and the estimated probability of prior censoring. Creating the IPTCWs requires estimating inverse probability of treatment weights (IPTWs), inverse probability of censoring weights (IPCWs), and stabilization weights.

To estimate the IPTWs, a series of logistic regression models will be used to estimate the propensity of transition from one treatment state at time *t_i-1_* to a new treatment state at time *t_i_*. These analyses will be limited to participants who were HIV-negative at time *t_i_*, and the analyses will include time-invariant (ie, baseline) covariates, and time-varying covariates from time *t_i_* or earlier. Potential confounders to be included in the propensity score models of treatment status will be identified based on existing knowledge and based on exploratory analyses. Factors associated with PrEP acceptability among Thai young MSM and TGW include STI history, frequency of anal intercourse, HIV testing history, PrEP awareness, and insurance status [13], and factors associated with PrEP acceptability in other populations include perceived risk for HIV, use of condoms, sexual identity, education, concerns about PrEP use, and sex with casual or exchange partners [43]. Based on the estimated coefficients, the predicted probability of the observed treatment will be estimated, and this estimate will be inverted to give the inverse probability of the observed treatment at time *t_i_*, given the observed treatment at time *t_i-1_*. Prior treatment history will be incorporated by multiplying the predicted probability of treatment by the probabilities of not receiving the observed treatment at each of the previous time points.

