Stabilization weights will be similarly estimated, but, in contrast, they will be based on logistic regression models including only time-invariant covariates. The IPTWs will be multiplied by the stabilization weights to improve their performance. The IPCWs will be similarly estimated and stabilized, but using transition from observed to unobserved in place of transition between PrEP use and nonuse, and the covariates used for the censoring model may differ from the covariates used in the treatment model. Finally, the product of the stabilized IPTWs and the stabilized IPCWs will provide the IPTCWs that will be used in the pooled logistic regression model to estimate the hazard ratio of HIV infection during time on PrEP and time off PrEP. The pooled logistic regression will include all time-invariant covariates used to create the stabilization weights and additional time-invariant covariates may be identified through exploratory data analysis.

The estimated log-odds of HIV infection and the standard error of the estimate from the pooled logistic will be used to evaluate whether the hazard of HIV differs between time on PrEP and time off PrEP, with the null and alternative hypotheses evaluated using the Wald statistic.

H10: The hazard of HIV during time on PrEP will not differ from the hazard of HIV for time not on PrEP: HIV hazard ratio=1.

H1a: The hazard of HIV during time on PrEP will differ from the hazard of HIV for time not on PrEP: HIV hazard ratio1.

The simplified primary outcome analysis will be conducted using Poisson regression, following the methods used by Grant et al [38]. The simplified analysis will have the benefit of easier interpretation but lack the ability to control for time-varying confounders that may be both causes and consequences of PrEP use (eg, sexual risk behavior and risk compensation).

The Poisson regression model will control for baseline covariates and include a time-varying indicator for PrEP status. The outcome will be assessed using a person-time approach, assessing HIV incidence densities among young MSM and TGW on and off daily oral PrEP over follow-up. In the Poisson regression, the Wald statistic will be used to evaluate the coefficient for PrEP status to distinguish between the null and alternate hypotheses.

H10: The HIV incident rate during time on PrEP will not differ from the incident rate for time not on PrEP: HIV incident rate ratio=1.

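### The rule for carrying past treatment into the marginal structural model weights is misstated and contradicts the article's own definition; coded as written, it would give degenerate weights

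*Protocol article*

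**What the plan says.** All of this is in the protocol article, Methods, Data Analysis, unless noted.

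- **Target of the weights.** The combined weights "incorporate the estimated probability of the observed treatment history and the estimated probability of prior censoring".
- **Models.** Logistic regressions "estimate the propensity of transition from one treatment state at time" t_i-1 to a new state at t_i.
- **Current week.** The predicted probability of the observed treatment is obtained, and "this estimate will be inverted to give the inverse probability of the observed treatment at time" t_i, given the treatment at t_i-1.
- **Earlier weeks.** Prior history enters by "multiplying the predicted probability of treatment by the probabilities of not receiving the observed treatment at each of the previous time points". No other sentence says how the weekly probabilities are accumulated.
- **Stabilization.** "Stabilization weights will be similarly estimated, but, in contrast, they will be based on logistic regression models including only time-invariant covariates".
- **Censoring.** "The IPCWs will be similarly estimated and stabilized", using the transition from observed to unobserved in place of the PrEP transition.
- **Time unit.** In the analysis file "each record represents 1 person-week of time either on PrEP or not on PrEP".
- **Exposure pattern (Study Visits).** "Participants can initiate, discontinue, and restart PrEP at any point during the study period".

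The section describes the marginal structural model as the more complex of two primary outcome analyses and ties it to published marginal structural model methods. The simplified analysis is a Poisson regression with baseline covariates and a time-varying PrEP indicator.

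**The concern.** An inverse-probability-of-treatment weight is the reciprocal of the probability of the treatment path a person actually followed. That probability is a product over weeks, and each factor is the probability of what was observed that week. The sentence on earlier weeks uses the complement instead: for each past week, the probability of what did not happen. In a weekly file where most people stay in the same state from one week to the next, each correct factor is close to 1 and each complement is close to 0. A year of follow-up multiplies about 51 of them.

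PrEP is self-selected, and the article says that its Poisson model cannot control time-varying confounders that are both causes and consequences of PrEP use. The marginal structural model is therefore the primary analysis meant to deal with that problem. The number of infections averted in the cost-effectiveness analysis is also taken from the primary outcome analyses. A published formula for this estimator that contradicts its own definition cannot be reproduced or audited.

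**Working it through.** The article gives no figure for the weights, so there is none to reproduce. It also gives no weekly switching rates, so those below are assumptions.

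**Notation.** Let p_k be the predicted probability of the treatment observed in week k, given the state in week k-1 and covariates.

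- Denominator implied by the definition (observed history): D_t = p_1 × p_2 × … × p_t. The weight is 1/D_t.
- Denominator by the sentence as written: L_t = p_t × (1 − p_1) × … × (1 − p_(t−1)). The weight is 1/L_t.

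**Step 1: 12 weeks in one state, assumed p = 0.99 each week.**
- D = 0.99^12 = 0.886, weight 1.13.
- L = 0.99 × 0.01^11 = 9.9e-23, weight about 1e22.

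**Step 2: 52 weeks in one state, assumed p = 0.98.**
- Correct: 1/0.98^52 = 2.86.
- As written: 1/(0.98 × 0.02^51) = 4.5e86.

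**Step 3: does stabilization repair it?** Build the numerator by the same rule, with 0.98 per week from the baseline-covariate model, over 52 weeks:

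| Weekly denominator probability | Correct stabilized weight | As-written stabilized weight |
|---|---|---|
| 0.98 | 1 | 1 |
| 0.99 | (0.98/0.99)^52 = 0.59 | (0.98/0.99) × (0.02/0.01)^51 = 2.2e15 |
| 0.97 | (0.98/0.97)^52 = 1.70 | (0.98/0.97) × (0.02/0.03)^51 = 1.1e-9 |

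The two rules agree only when covariates add nothing. Otherwise the as-written weight is extreme and moves in the wrong direction: a person who should be weighted down is weighted up, and the reverse.

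**Step 4: where the wording does fit.** Take someone off PrEP for 11 weeks who starts in week 12, with an assumed weekly start probability of 0.01. The correct history is 0.99^11 × 0.01 = 0.00895. If the treatment in the sentence is the new state, the probability of not receiving it earlier is 0.99 per week, and the sentence gives the same 0.00895. One week later the person stays on PrEP with probability 0.99. The correct value is 0.00895 × 0.99 = 0.00886. Multiplying by the probabilities of not having moved to PrEP in weeks 1 to 12 gives 0.99 × 0.99^12 = 0.878, which is 99 times too large. So the rule breaks after the first switch even on this reading.

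**Step 5: which pattern matters here.** The Results (Combination Prevention Intervention) report that 330 of 445 participants started PrEP at baseline, with 134 of about 168 person-years adherent. Long unbroken spells, as in Steps 1 to 3, are therefore likely to be common.

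**Step 6: illustrative simulation.** There were 150 datasets of 1240 people over 52 weeks. From the article: incidence of 8.5 per 100 PY off PrEP and a 50% reduction (used as the direct rate ratio, 0.5). Assumed: one binary time-varying confounder, its strength, and switching of about 1% to 3% per week. The hazard ratio was taken as the weighted rate ratio, which is close to the pooled logistic odds ratio at these small weekly hazards.

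| Weights | Largest weight (median) | Effective share of person-weeks | HR, 5th to 95th percentile |
|---|---|---|---|
| Correct, stabilized | about 5 | 85% | 0.36 to 0.82 |
| As written, stabilized | about 5e11 | 0.27% | 0.0006 to 1900 |
| As written, unstabilized | about 1e98 | 0.04% | 1e-14 to 4e10 |

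A single run of 200,000 people gave an HR of 0.55 with correct weights, 0.65 unweighted and 1.11 with the as-written stabilized weights. A second simulation, with 20 datasets of 4000 people and other assumptions, gave the same picture for stabilized weights: effective sample 95% with correct weights against 0.04% as written, and HRs of 0.40 to 0.60 against 0.009 to 74.

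**The case against.** The strongest reply is that this is one faulty sentence in a condensed article whose surrounding text is right. The target is stated correctly, the current-week probability is inverted correctly, and a published method is named. The models are described as models of transition, and in that language a product of probabilities of not yet having switched is the right history up to a first switch. Weights of 1e9 or more would be noticed at once, so a silent error in the reported result is unlikely.

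Most of this stands, and it limits the point in three ways.

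- A reader might infer that the analysis will produce degenerate weights. The document does not support that. It would happen only if the sentence were coded literally, against the definition beside it.
- A reader might infer that the censoring weights carry the same error because they are estimated similarly. The document does not support that either. Moving from observed to unobserved is a one-way transition, and a product of probabilities of not yet being censored is correct for it.
- A reader might infer that the whole primary comparison fails. The Poisson form does not use these weights and is untouched.

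What does not stand is the idea that the sentence is harmless. It is the only instruction on accumulation, so a programmer following the steps would reach it. The first-switch reading departs from the words for anyone who simply continues in one state. It also fails after the first switch (Step 4), although the study expects people to stop and restart. Nor is this detail left to a fuller document: the article states the rule, and states it wrongly.

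**Conclusion.** The Data Analysis section misstates how prior treatment history enters the treatment weight and contradicts its own definition. A drafting slip is the more likely explanation, but as written the rule is wrong for weeks spent continuing in one state and for repeated switching. Literal coding would make the treatment weights, and the stabilization weights built the same way, degenerate, and the marginal structural model hazard ratio would be uninterpretable.

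The closed-form example (about 1e-22 against 0.886 over 12 weeks) depends only on the assumed 0.99 per week. The simulation figures depend also on assumed switching rates and confounder strength. They show the kind of failure, and that stabilizing by the same rule does not cure it, but they do not predict this trial's numbers. The Poisson analysis is unaffected but is no substitute, because it cannot control time-varying confounding.

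**What to change.** Replace the sentence on prior history with wording such as: the denominator of the treatment weight at t_i is the product, over all weeks up to and including t_i, of the predicted probabilities of receiving the treatment actually observed in that week, given the previous state and covariates; the weight is the inverse of this product. Add that the stabilization numerator is the same product computed from the models with baseline covariates only.

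For clarity, also state that the censoring weight uses the product of the probabilities of remaining uncensored. The present transition wording can already be read this way, so this is not the correction of a separate error.

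Then check that the analysis code follows the corrected rule. The cost is a sentence or two and a code check, with no change to data collection or study conduct.

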**Methods:**

This open-label, nonrandomized assessment compares the relative effectiveness of a combination prevention intervention with and without daily oral emtricitabine and tenofovir disoproxil fumarate (Truvada) PrEP with SMS-based adherence support. HIV-uninfected young MSM and TGW aged 18 to 26 years in Bangkok and Pattaya who self-report selling/exchanging sex at least once in the previous 12 months are recruited by convenience sampling and peer referral and are eligible regardless of their intent to initiate PrEP. At baseline, participants complete a standard assessment for PrEP eligibility and may initiate PrEP then or at any time during study participation. All participants complete a survey and HIV testing at baseline and every 3 months. Participants who initiate PrEP complete monthly pill pickups and may opt-in to SMS reminders. All participants are sent brief weekly SMS surveys to assess behavior with additional adherence questions for those who initiated PrEP. Adherence is defined as use of 4 or more pills within the last 7 days. The analytic plan uses a person-time approach to assess HIV incidence, comparing participant time on oral PrEP to participant time off oral PrEP for 12 to 24 months of follow-up, using a propensity score to control for confounders. Enrollment is based on the goal of observing 620 person-years (PY) on PrEP and 620 PY off PrEP.

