### Intervention Effectiveness Study Design

The study is an open label, nonrandomized assessment comparing the relative effectiveness of a combination preventive intervention with and without daily oral tenofovir/emtricitabine (FTC; Truvada) PrEP with adherence support. We follow those young MSM and TGW who choose to initiate PrEP as part of the combination package, and those who agree to participate but do not choose to start on PrEP, for whom all other intervention components will be offered. The outcome will be assessed using a person-time approach, assessing HIV incidence densities among young MSM and TGW on and off daily oral PrEP over 12 to 24 months of follow-up. Participants are enrolled for a standard follow-up period of 12 months; however, given the importance of remaining on PrEP for people in high-risk contexts, we offer the option to re-enroll for an additional 12 months. All participants, regardless of PrEP status complete quarterly study visits and weekly, brief behavioral SMS surveys. Participants who initiate PrEP are required to attend monthly medication pickup visits. Figure 1 displays the flow diagram of the study with a brief description of study visit activities.

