### Sample Size Calculation

This study focuses on the primary endpoint of incident HIV infection during follow-up, comparing person-time on PrEP and off PrEP. Participant uptake of PrEP, level of PrEP adherence, and cessation of PrEP use serve as secondary endpoints in this study.

As prospectively measured in the Bangkok MSM Cohort Study cohort [37], we expect that the participants will be a mixture of very high-risk MSM and TGW 18 to 24 years of age with an HIV incidence rate of 11 per 100 PY and high-risk MSM 22 to 26 years of age with an incidence rate of 5 per 100 PY. Assuming a 50/50 mixture, we expect an incident rate of 8.5 per 100 PY (range=7-10). On the basis of recent iPrEx open-label extension (iPrEx OLE) study, we assume a 50% reduction in incidence for the PrEP group versus off-PrEP group [38]. On the basis of empirical evidence, we expect that some 50% of the participants will choose to take PrEP.

The sample size of this study is 1240 participants based on the following assumptions: incidence without PrEP is 8.5 per 100 PY, a PrEP efficacy of 50%, time-on-PrEP of 50%, attrition of approximately 2% per month, power=0.8, α (one-sided)=.025, and inflation of the standard error of the hazard ratio by 0% to 20% after adjusting for confounding. From this assumption, we expect that a combined sample of 1240 (620 on PrEP and 620 not on PrEP) will be sufficient.

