### Combination Prevention Intervention

As of February 2019, 445 participants (417 MSM and 28 TGW) have contributed approximately 168 PY with 95% (73/77) retention at 12 months. 74.2% (330/445) of enrolled participants initiated PrEP at baseline, contributing to 134 PY of PrEP adherence based on a measure of 4 or more pills within the last 7 days, 1 PY nonadherence, and 33 PY PrEP nonuse/noninitiation. Monitoring of unexpected events has identified 7 social harms, predominantly related to unintentional participant disclosure of PrEP use and peer stigmatization of PrEP and HIV.

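### The Wald statistic fixed for both primary tests is unusable if no infection occurs on PrEP, and the protocol article names no alternative test

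*Protocol article*

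**What the plan says.** The Data Analysis section describes two primary analyses of HIV incidence on versus off PrEP. For the weighted pooled logistic (marginal structural) model, the log-odds estimate and its standard error from that fit are used, "with the null and alternative hypotheses evaluated using the Wald statistic". For the simplified Poisson model, "the Wald statistic will be used to evaluate the coefficient for PrEP status". The article names no likelihood-ratio, score, exact or penalised test, and gives no rule for a PrEP state without infections.

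The planning inputs in Sample Size Calculation are "incidence without PrEP is 8.5 per 100 PY, a PrEP efficacy of 50%, time-on-PrEP of 50%, attrition of approximately 2% per month", with "power=0.8, α (one-sided)=.025, and inflation of the standard error of the hazard ratio by 0% to 20% after adjusting for confounding". The abstract states the target as the "goal of observing 620 person-years (PY) on PrEP and 620 PY off PrEP". Interim data (Results, Combination Prevention Intervention) show 330 of 445 participants starting PrEP at baseline, "contributing to 134 PY of PrEP adherence based on a measure of 4 or more pills within the last 7 days", plus 1 PY of nonadherence and 33 PY of nonuse. Infection counts are not reported.

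**The concern.** A Wald test divides an estimate by its standard error. When one group has no events, the log ratio runs to minus infinity and its model-based standard error grows faster, so the statistic goes to zero. The rule would then return no evidence of a difference from what may be very strong data, with no usable confidence interval. Choosing another test after seeing zero events would be a post hoc change to the primary analysis of a nonrandomised study, where that is hard to defend.

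**Working it through.** **1. The plan's own figure.** Schoenfeld events for a hazard ratio of 0.5, one-sided 0.025, power 0.80 and a 50/50 split: 4 × (1.960 + 0.842)² / (ln 2)² = 65.35. With a 10% standard-error inflation (the middle of the stated 0–20%): 65.35 × 1.21 = 79.1. Dividing by the mean rate, (8.5 + 4.25)/2 = 6.375 per 100 PY, gives 1240 PY. So 1240 reproduces as person-years. It implies 620 × 0.0425 = 26 infections on PrEP and 620 × 0.085 = 53 off PrEP. With those counts a Wald test is adequate.

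**2. Zero infections on PrEP, Poisson model.** The interim split is 135/168 = 80% on PrEP. Applied to 1240 PY this gives 992 on and 248 off, with 248 × 0.085 = 21 infections off PrEP.
- Wald: coefficient about −24.8, standard error about 15,800, p = 0.999. The coefficient only reflects where the iterations stopped.
- Likelihood ratio: 2 × 21 × ln(1240/248) = 42 × 1.609 = 67.6 on 1 df, p = 2e-16.
- Exact upper 97.5% limit: pU = 1 − 0.025^(1/21) = 0.161; (0.161/0.839) × (248/992) = 0.048.
- Profile-likelihood upper limit (two-sided 95%): 1 − p = exp(−3.84/42) = 0.913; (0.087/0.913) × 0.25 = 0.024. It is finite, though tighter than the exact limit.

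Other splits behave the same way. For 0/480 against 10/120 PY, Wald p is 0.999, likelihood-ratio p 1e-8 and the exact upper limit 0.11. For 0/620 against 53/620 PY, Wald p exceeds 0.999, likelihood-ratio p is 1e-17 and the exact upper limit 0.07. All of these are unadjusted.

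**3. Zero infections on PrEP, pooled logistic model.** Simulated person-week records were used: 620 participants per state, 52 weeks each, one covariate, 0 against 53 events.

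| Standard error | Coefficient | SE | Wald p |
|---|---|---|---|
| Model-based | −24.2 | 14,655 | 0.9987 |
| Model-based, tighter convergence | −30.8 | 373,751 | 0.9999 |
| Participant-clustered sandwich | −24.2 | 0.138 | essentially 0 |

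The sandwich value is close to 1/√53 = 0.137: it carries only the off-PrEP variation, because on-PrEP records have almost no residuals. Adding weights did not change the pattern.

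**4. One infection on PrEP.** For 1/992 against 21/248 PY: ln(1/84) = −4.43, SE = √(1 + 1/21) = 1.02, p = 1.5e-5, upper limit 0.09. For 1/480 against 10/120 PY: p = 0.0004, upper limit 0.20. The Wald test works again.

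**5. Probability of exactly zero.** P(0) = exp(−PY × 0.085 × (1 − reduction)). The 8.5 per 100 PY and the 50% reduction are the plan's; 90% and 95% are assumptions made here.

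| On-PrEP PY | 50% | 90% | 95% |
|---|---|---|---|
| 300 | 3e-6 | 8% | 28% |
| 620 | 4e-12 | 0.5% | 7% |
| 992 | 5e-19 | 0.02% | 1.5% |

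**The case against.** Wald is a conventional default and suits the effect the study was designed for. The only reduction the document assumes is 50%, under which zero events will not happen. A sparse-data fallback is commonly left to an analysis plan, which is not shown. Both points stand, and they limit how serious this is. They do not remove it: the article names a specific test twice, so the issue is a stated rule that breaks in one outcome, not an omitted detail.

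Several stronger readings are tempting, and the documents do not support them.
- A reader might infer that both primary tests would return p near 1. For the weighted model that holds only with a model-based standard error. The article does not say model-based or robust; with a clustered sandwich the error runs the other way.
- A reader might infer that very few on-PrEP infections are enough to break the test. They are not; it takes exactly zero.
- A reader might take 134 adherent PY out of 135 as showing that zero events is likely. Adherence is at least 4 pills in 7 days, with weekly doses self-reported by SMS. Drug levels are assayed only in participants prescribed PrEP who seroconvert. Two consecutive low-dose weeks count as stopping (Study Visits), which can itself keep nonadherent time small.
- A reader might infer that the infections-averted input would lose its interval. Cost-Effectiveness Analysis defines it as expected minus observed infections, which exists when the observed count is zero, and draws uncertainty intervals from primary data, literature and expert opinion.
- A reader might want an exact test as the primary analysis. It would drop the baseline covariates that the Poisson model adjusts for, in a study where participants select themselves into PrEP.

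**Conclusion.** The point holds, conditionally. With exactly zero on-PrEP infections, the Poisson Wald test with its model-based standard error gives p near 1 and no usable interval. The weighted pooled logistic Wald test is invalid in a direction that depends on the standard error chosen. With one or more on-PrEP infections the stated rule functions. The condition is remote under the planned 50% reduction. It becomes a real possibility only if the true reduction is much larger or on-PrEP time falls well short of 620 PY. The larger reductions are assumptions, and the comparison p-values and limits are unadjusted, so they show that the test breaks down and do not establish a causal effect. This is a worthwhile correction to make before outcome data are seen, and no threat to the design.

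**What to change.** In Data Analysis:
- **Poisson model.** Test the PrEP coefficient in the covariate-adjusted model by the likelihood-ratio test and report a profile-likelihood interval, which still gives an upper limit when on-PrEP infections are zero. Keep an exact conditional test and limit only as an unadjusted supporting analysis; with zero events its limit is the more cautious one (0.048 against 0.024 in the example above).
- **Weighted pooled logistic model.** State that if either PrEP state has no infections, a Firth-penalised weighted estimate or a participant-clustered score test replaces Wald, and say in advance which of the two decides. State also which standard error is used otherwise.

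The cost is a few sentences and a little more analysis work. The sample size is unchanged, and with ample events the results barely move.
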